## Intervention

A collaborative effort between a group of experienced psychologists and the first author, [name], who is a medical doctor, led to the development of the intervention manual. Drawing from the literature presented in the introduction, the intervention was constructed around four elements:*Setting*: The training takes place on-site, which enables context-specific feedback tailored to the clinical scenario and eliminates transfer of acquired skills from a training environment to the workplace [30, 31].*Format/pedagogical tools*: Training is focused on individual objectives defined as learning goals and will be based on direct feedback and reflection [20, 21].*Duration*: The training program lasts three full working days [18]. Although not labeled “follow-up training” [18] the 3–4-week gap between intervention days is designed to foster skill development between sessions.*Facilitation by trained psychologists* [29]: All psychologists are experienced and have read the intervention manual carefully, thereby ensuring fidelity to the intervention. During the intervention period, psychologists receive regular supervision from an experienced psychologist.

### Structure of the intervention days

The psychologists will observe doctor-patient consultations for one full working day at a time (intervention day). At the time of randomization, psychologists are assigned to the same doctors throughout the intervention period. Prior to the first intervention day two one-hour sessions are held by the psychologist for all doctors randomized to the intervention before the first intervention day. The first session is preferably a group meeting where the doctors are introduced to their psychologist, expectations are aligned, and they get acquainted with the term “learning goals”. The second session is preferably individual, where the doctor and the psychologist start the process of formulating one or two learning goal(s).

On intervention days, the psychologist and the doctor agree on a learning goal for the On-site SCT. A time slot of 30 to 45 min is allocated for feedback after completion of three to four consultations, and at the end of the day there is a 60-min session for more thorough feedback and planning. The plan will serve as a guide to refining strategies during the interim period until the next intervention day.

It is expected that the doctor can be scheduled with six to seven consultations on an intervention day (cf. up to 12 normally). The psychologist will attend the consultations as an observer only. After all intervention days, the psychologist will register data in REDCap, documenting the number of patients seen, time spent on feedback, the psychologist's assessment of the doctor's motivation, and the learning goals set by the doctor. The intervention period for each doctor is 3–4 months as illustrated in Fig. 2.

**Fig. 2 Fig2:**
[figure not shown]
*Overview of the intervention.*On-site SCT: On-site Supportive Communication Training

### Theoretical framework of the intervention

The purpose of the intervention is to contribute to doctors' continuing professional development, focusing specifically on improved doctor-patient communication and increased self-awareness. This will be achieved through reflection on consultation practices aligned with communication knowledge gained from the 3-day On-site SCT.

The intervention manual was designed to cover the following elements: I) *Communication.* Doctors are intended to become better at communicating, including using patient-centered communication focusing on the needs and emotions of the patients. II) *Learning to learn.* Doctors are encouraged to enhance their ability to identify and explore their own learning needs. This process involves formulating “learning goals” and experimenting with new approaches to engage in conversations with patients. III) *Compassion.* Doctors are aimed to gain better insight into their own reactions/emotions and through psychoeducation be introduced to a compassion-based approach to the doctor‒patient relationship and communication.

### Theoretical frameworks of communication

The description of skills for communication with the patients is rooted in the framework of the Calgary-Cambridge Guide [34, 35]. It outlines evidence-based microskills associated with each of the five domains of the consultation process, i.e. initiating the session, gathering information, providing explanations, making plans, and closing the session. The Calgary-Cambridge Guide also describes how to provide structure to the consultation and build a relationship with the patient.

### Theoretical frameworks of learning

This part is grounded in theories of action research [36], which itself builds on action learning, a pedagogical concept asserting that individuals learn most effectively when taking part in formulating what they would like to learn and when tackling real-time problems within their own work environment [37]. Action research involves an additional layer of awareness that facilitates the deliberate questioning of existing perspectives and interpretations – a process often termed double loop learning as depicted in Fig. 3 [38, 39]. It explores how individuals can benefit from reflecting on assumptions, actions, and underlying values, often eliciting tacit knowledge [40].

**Fig. 3 Fig3:**
[figure not shown]
Single vs. double looped learning

As illustrated in Fig. 4 (adapted from Altrichter et al. [36]), the initial sessions (group and individual) in On-site SCT enable doctors to define their initial *learning goals* (Cycle 1). Through the psychologist's observation of the doctor's interaction with the patient, a collaborative reflection opportunity emerges. The joint reflection aims to deepen the doctors' comprehension of their practices (double-loop learning) and, if applicable, to develop novel approaches and strategies to be tested in a subsequent learning cycle.

**Fig. 4 Fig4:**
[figure not shown]
Learning cycles in On-site Supportive Communication Training

The project design facilitates different levels of reflection [41]:Reflection-on-action occurs after an event to assess actions and outcomes.Reflection-for-action focuses on improving future practices.Reflection-in-action takes place during an event, enabling real-time adjustments.

During intervention days, most reflections are likely reflection-on-action and reflection-for-action, where psychologists and doctors reflect on specific doctor-patient interactions to establish a revised plan.

The period of 3–4 weeks between intervention days allows for practitioners to engage in reflection-in-action. As described by Schön [42], this reflective practice involves the dynamic assessment and adjustment of one's actions in response to evolving insights during a given situation. It essentially entails a form of metacognition, where individuals actively monitor and adapt their actions based on their developing understanding of the context. According to Schön, the process is most impactful when it arises in response to disruptions in established patterns, which can occur when doctors receive feedback from psychologists regarding communication strategies and routines.

### Theoretical frameworks of compassion

The CST used in the current study is termed "supportive" because all psychologists operate on a compassion-based foundation. Compassion is often defined as “a sensitivity to suffering in oneself and others, with a commitment to try to alleviate and prevent it” [43]. Suffering is often present in patients due to their diagnosis, but it can also be present in doctors, for example when they feel inadequate due to lack of time, when the disease is incurable, or when a patient is experiencing a crisis. The doctors do not undergo training in compassion-focused therapy [44] as part of the On-site SCT, but psychologists may provide psychoeducation rooted in the framework of compassion-focused therapy, when relevant for the doctor. The aim is to assist the doctors in their encounters with patients as well as in their role as medical practitioners. In the process of eliciting learning goals and engaging in reflective practices as a component of double-looped learning, compassion-focused therapy plays a significant role in uncovering doctors’ underlying motivations, emotions, and values.

Qualifications of project psychologistsThe psychologists conducting On-site SCT have experience working with patients in an oncology department. Additionally, they are knowledgeable about the Calgary-Cambridge model for effective medical communication and shared decision-making. The psychologists themselves have undergone more than 100 h of supervision during their psychological training. In connection with the project, they participated in a four-day joint training/start-up meeting covering all aspects of the intervention. Furthermore, the psychologists receive collective supervision every three weeks throughout the project period.

### Experiences from a feasibility trial

An initial version of the intervention manual was tested and adapted in a feasibility trial involving four doctors at the Department of Oncology, Herlev Hospital, Denmark. They all participated in one day of On-site SCT conducted by a psychologist (second author). The feasibility and relevance of the intervention was investigated by interviewing the participating doctors. The interviews were conducted by the first author, [name]. The following observations were made during the trial days and interviews:

*Feasibility*: The intervention was feasible within the designated timeframe and available resources. The presence of the psychologist was well received by doctors and patients, and no patients declined the presence of the observer.

*Relevance and adaptation*: All doctors responded positively to the concept of establishing their individual learning goal(s). It became evident that concentrating on one goal at a time was preferable, as a broader focus made the feedback too abstract within the one-day period.

*Overall experience*: The doctors found the intervention valuable and meaningful recognizing its potential in improving their communication skills.

## Primary outcome measure (patients)

The effect of On-site SCT on patients’ evaluation of the doctors’ communication skills is assessed by the 15-item Communication Assessment Tool (CAT). It is a reliable and valid instrument for measuring patient perceptions of physician performance in the area of interpersonal and communication skills [32]. Since its last item, “The doctor’s staff treated me with respect”, is focused on the staff, it will not be included in this study. The questionnaire was validated in 2007 with a sample of 40 doctors from six distinct medical boards [32]. Later it was translated to Danish and validated to assess the perspectives of Danish patients on clinicians' communication skills [33].

## Secondary outcome measures (doctors)

At baseline and evaluation all participating doctors at the three departments are asked to fill out questionnaires measuring communication self-efficacy, degree of burnout, and job satisfaction.

Self-efficacy in Health Communication (SE-12) consists of 12 questions eliciting healthcare professionals’ perceived self-efficacy in communication with patients. The questionnaire was developed and validated by Axboe et al. [45]. Parts 2 and 3 of the “Copenhagen Burnout Inventory (CBI)” assess work and patient-related burnout, respectively. The questionnaire has been validated in seven types of workplaces, including doctors at a somatic hospital [46]. In the Region of Southern Denmark job satisfaction is measured among 25,000 healthcare workers in a survey every other year, thus offering a large amount of comparable data. Five items on job satisfaction are extracted from the survey for the present study.

## Statistical analysis plan

All statistical analyses will be performed in close collaboration with a statistical consultant based on predefined statistical analysis plans. A 95% confidence interval is applied. P values < 0.05 are considered statistically significant. STATA version 18 will be used for all analyses, and all steps of data management, coding and analysis will be logged.

### Primary endpoint

The primary outcome measure is the change in percentage of “excellent” scores measured by the CAT questionnaire on each of the 14 items. All items are answered on a numerical scale from 1 (poor) to 5 (excellent), as well as the option "not relevant". The difference in percentage of "excellent" scores between patients treated by doctors in the intervention and control groups will be analyzed by binary regression using robust variance estimation and taking clustering of patients seeing the same doctor into account. The model will include participating site as a covariate. Due to the randomization and the high number of observations, exchangeability is expected between the patients in the two study groups, and hence, no further covariates are planned in the model. Exchangability will be investigated using standardized differences. A standardized differences > 0.1 indicate imbalance between groups. Effects will be reported on relative and absolute scales as relative risk (RR) and risk differences (RD).

Data will be collected from the patients’ questionnaires on sociodemographic information, years with cancer, disease stage (curable, incurable, unknown), relation to the doctor (first meet or not), and participation or not of relatives at the consultation. Subgroup analysis stratified by site will be performed.

All analyses will be evaluated as intention to treat. The proportion of missing data in the patient questionnaires will be investigated. If the proportion is less than 5%, a complete case analysis will be performed. If missing data exceeds 5%, an imputation analysis will be applied [47].

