**Methods:**

This randomized multicenter trial is conducted at three departments of oncology in Denmark. Doctors are randomized 1:1 to the intervention and control groups. The intervention group involves participation in three full days of On-site SCT facilitated by a trained psychologist. On-site SCT focuses on imparting communication techniques, establishing a reflective learning environment, and offering emotional support with a compassionate mindset. The primary endpoint is the change in percentage of items rated “excellent” by the patients in the validated 15-item questionnaire Communication Assessment Tool*.* The secondary endpoints are changes in doctors’ ratings of self-efficacy in health communication, burnout, and job satisfaction measured by validated questionnaires. Qualitative interviews will be conducted with the doctors after the intervention to evaluate its relevance, feasibility, and working mechanisms. Doctors have been actively recruited during summer/autumn 2023. Baseline questionnaires from patients have been collected. Recruitment of new patients for evaluation questionnaires is scheduled for Q1-Q2 2024.

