## Sample size calculation

Approximately 80 out of the around 90 eligible doctors (89%) are expected to participate in the study.

To achieve a power of 80%, a sample size of 2,080 patients (1,040 in each group) will be obtained by sampling 40 clusters (doctors) with 26 patient questionnaires in each group. In total we thus aim to collect 4160 questionnaires. The proportion in the intervention group is assumed to be 0.28 under the null hypothesis and 0.34 [33] under the alternative hypothesis assuming a difference between the group proportions of 0.06. Due to the lack of international consensus in this research area, an absolute change of 6% was agreed upon by mutual consensus in the steering group, as we believe such change would represent a clinical relevant difference for the patients. The proportion in the control group is assumed to be 0.28. The sample size calculation is based on a two-sided Z Test (unpooled) with intracluster correlation (ICC) set at 0.005, and significance level of the test at 0.05.

Each cluster size of 26 completed questionnaires per doctor at baseline and evaluations aligns with the recommendations from the CAT developers [32]. To meet the target we aim to distribute 30–40 questionnaires per doctor. Staff at each outpatient clinic will assist in the process.

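### The abstract makes the primary endpoint one percentage across items and the analysis section makes it a percentage on each of 14 items; read literally, the second means 14 primary tests at 0.05 with no correction stated

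*Protocol article*

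**What the plan says.** All places are in the protocol article.

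- **Abstract, Methods.** The primary endpoint is the "change in percentage of items rated “excellent” by the patients in the validated 15-item questionnaire". This is one summary percentage taken across items.
- **Primary endpoint.** The outcome is the change in the percentage of excellent "scores measured by the CAT questionnaire on each of the 14 items". This is a proportion for each item. The section then describes, in the singular, a "binary regression using robust variance estimation and taking clustering of patients seeing the same doctor into account", with results given as RR and RD. It does not say whether the modelled outcome is one item at a time, all items stacked, or a summary per patient.
- **Statistical analysis plan.** The general rule is: "P values < 0.05 are considered statistically significant". The article names no lead item and no adjustment for several primary tests.
- **Sample size calculation.** "The proportion in the intervention group is assumed to be 0.28 under the null hypothesis and 0.34" under the alternative, with 0.28 in the control group and "a sample size of 2,080 patients (1,040 in each group) will be obtained by sampling 40 clusters (doctors) with 26 patient questionnaires" in each group. The section does not say what these are proportions of.
- **Discussion, Strengths.** The endpoint appears again as a change in the percentage of excellent scores, which fits either wording.

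**The concern.** A percentage pooled over items and a set of 14 item percentages are different primary variables. The first gives one test. The second gives 14, and nothing in the article stops a significant difference on any one item from being presented as a positive primary result. The two can also disagree: a few items may move while the pooled percentage does not, or a modest shift across all items may be clear when pooled and unclear item by item.

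The power statement depends on the same choice. It was computed for one binary result per patient and one test, so what the 80% refers to changes with the reading. The trial is unblinded by its own account (Limitations), which makes a single fixed primary test more valuable.

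**Working it through.** **Inputs from the article:** control proportion 0.28; intervention proportion 0.34; difference 0.06; ICC 0.005; 26 questionnaires per doctor; 40 doctors and 1,040 patients per group; two-sided unpooled Z test at 0.05; power 80%; 14 items analysed.

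**Assumed, because the article gives no figure:** the correlation between the 14 item test statistics (0 to 0.9), and the correlation r between items within a patient (0.3 to 1).

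**1. The plan's own figure**

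- Variance sum: 0.28 × 0.72 + 0.34 × 0.66 = 0.2016 + 0.2244 = 0.4260.
- Unadjusted n per group: (1.960 + 0.842)² × 0.4260 / 0.06² = 928.8.
- Design effect: 1 + (26 − 1) × 0.005 = 1.125.
- Adjusted n per group: 928.8 × 1.125 = 1,045, against 1,040 stated.
- Standard error at 1,040: √(0.4260 × 1.125 / 1,040) = 0.02147.
- Power: Φ(0.06 / 0.02147 − 1.960) = 79.8%.

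The figure reproduces with one yes/no result per patient and one test at 0.05.

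**2. Item-by-item reading: 14 tests at 0.05**

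Under independence the chance of at least one false positive is 1 − 0.95¹⁴ = 51.2%. For equally correlated normal test statistics (400,000 simulated sets):

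| Assumed correlation | At least one p < 0.05 |
|---|---|
| 0.3 | 43.8% |
| 0.5 | 34.8% |
| 0.7 | 24.8% |
| 0.8 | 19.7% |
| 0.9 | 14.0% |

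With Bonferroni, each item is tested at 0.05 / 14 = 0.00357. Power per item at 1,040 per group is then Φ(0.06 / 0.02147 − 2.91) = 45.3%. Restoring 80% per item would need about 1,877 per group, or 73 doctors with 26 questionnaires each.

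**3. Pooled reading: share of the 14 items rated excellent**

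With equal item correlation r, the variance per patient is (1 + 13r) / 14 of the binary variance. Keeping 0.28, 0.34 and ICC 0.005:

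| r | Variance factor | Power at 1,040 per group |
|---|---|---|
| 0.3 | 0.350 | 99.7% |
| 0.5 | 0.536 | 96.8% |
| 0.7 | 0.721 | 90.8% |
| 0.8 | 0.814 | 87.2% |
| 1 | 1.000 | 79.8% |

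This holds only if 0.005 is the right ICC for the pooled variable. The margin is used up when the variance factor times the design effect equals 1.125:

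- r = 0.8: the design effect may rise to 1.125 / 0.814 = 1.38, an ICC of (1.38 − 1) / 25 ≈ 0.015.
- r = 0.5: it may rise to 1.125 / 0.536 = 2.10, an ICC of 0.044.

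**The case against.** The best defence is that one endpoint was meant throughout. The abstract uses one percentage, the Primary endpoint section speaks of one difference and one model, the Hypotheses section has one patient-level hypothesis, and the sample size has one pair of proportions and one alpha. On that view, the mention of each item only says where the scores come from. The article also refers to predefined analysis plans, which are not shown and may settle how items are combined and how multiplicity is handled.

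Much of this stands, and it limits what may be claimed. A reader might infer several stronger things that the article does not support:

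- *Three conflicting definitions.* Only two are written. One binary result per patient is inferred from the sample size calculation.
- *A power calculation that matches no reading.* It matches a single item tested once.
- *An underpowered trial.* Under the pooled reading the calculation is conservative at the stated ICC.
- *A choice made after seeing the data.* The reference to predefined plans means this is not shown.
- *A false-positive risk of 51%.* That needs independent items, which is implausible for 14 ratings of one doctor by the same patient.
- *An item-count error in the abstract.* The phrase "by the patients in the validated 15-item questionnaire" describes the instrument, and the Primary outcome measure section explains why its last item is dropped.

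The defence does not remove the conflict itself. Two sections of one document word the primary variable differently, and an unseen plan that picks one must depart from the other. This is stated text in disagreement, not detail left to a later document.

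**Conclusion.** The point holds as a conflict between the abstract and the Primary endpoint section over the primary variable. Taken literally, the latter gives 14 primary tests at 0.05 with no lead item or correction in this document. The familywise error is then about 14% to 35%, conditional on that reading and on assumed correlations of 0.9 to 0.5 between test statistics.

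The sample size arithmetic is sound. Its weakness is that 0.28, 0.34 and the ICC are not tied to a named variable. The stated 80% is right for one item tested once, becomes about 45% per item if 14 items are tested with Bonferroni, and is a lower bound for the pooled percentage as long as ICC 0.005 applies to it. If the pooled percentage was intended, the trial loses nothing by saying so.

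**What to change.** Use one primary variable in the abstract, the Sample size calculation, the Primary endpoint section and the Discussion:

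- **Variable.** The pooled proportion of item responses rated 5 among those of the 14 items answered 1 to 5. Responses marked not relevant leave the denominator.
- **Analysis.** One test at two-sided 0.05: the planned binary regression on stacked item responses, with site as covariate and robust variance clustered on doctor, giving one RR and one RD. Clustering on doctor also covers the correlation between items from the same patient. Stacking keeps the outcome binary, as the planned model requires; a fraction per questionnaire would not, and it weights patients differently when some items are not relevant. The text should therefore name stacking explicitly.
- **Items.** Report the 14 item-level differences descriptively, with confidence intervals and no claim of significance.
- **Sample size.** Say that 0.28, 0.34 and the ICC refer to this variable, or give the values that do, and note that the stated 80% was computed for a single binary result per patient.

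The cost is wording in four places. No new data, patients or doctors are needed. If an analysis plan already fixes another single variable, the article should be aligned with it.

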## Methods

### Setting

This study is a randomized, controlled, multicenter study with three participating sites: Vejle Hospital, Aalborg University Hospital, and Zealand University Hospital. Hypotheses are tested by comparing questionnaires before and after the intervention.

Each site has a study coordinator to ensure adherence to the intervention protocol. The project employs seven experienced psychologists (one person-year in total).

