## Participants

### Patients

Patients attending a doctor's appointment at the outpatient clinic during the data collection periods are eligible to participate in the study. They will be encouraged to complete the Communication Assessment Tool (CAT) [32], a validated questionnaire, providing their evaluation of the doctor’s performance in the areas of interpersonal and communication skills. Each questionnaire is marked with the initials of the specific doctor, allowing for comparison between doctors in the intervention and control groups. When possible, questionnaires are distributed by study nurses or secretaries instead of the doctors themselves to reduce the risk of selection bias (i.e., the situation where doctors select the patients they hand a questionnaire). Questionnaires will be administered at baseline and evaluation. In case some patients do not wish to participate, their empty questionnaires will be collected to track the response rate.

Our aim was to collect questionnaires from all patients interacting with a doctor eligible for enrolment, as this approach will enable us to compare participating and nonparticipating doctors. Baseline questionnaires have been collected at all three sites during summer/fall 2023. The recruitment of new patients for evaluation questionnaires is scheduled for Q1-Q2 2024.

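### The primary endpoint is named as a change, but the model has no baseline or period term and the stated 80% power belongs to a between-arm comparison at one time point

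*Protocol article*

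**What the plan says.** **Endpoint.** The Abstract (Methods) states: "The primary endpoint is the change in percentage of items rated" excellent. The Primary endpoint section agrees: "The primary outcome measure is the change in percentage of" 'excellent' scores. The Strengths part of the Discussion uses the same term.

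**Test.** Under Setting: "Hypotheses are tested by comparing questionnaires before and after the intervention". Under Patients: "Questionnaires will be administered at baseline and evaluation". The same section says that new patients are recruited for the second round, so the design is two cross-sections of patients under the same doctors.

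**Model.** The Primary endpoint section says that the difference "between patients treated by doctors in the intervention and control groups will be analyzed by binary regression using robust variance estimation", with allowance for clustering by doctor. On covariates it says "The model will include participating site as a covariate" and "no further covariates are planned in the model".

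**Size.** The Sample size calculation says "a sample size of 2,080 patients (1,040 in each group) will be obtained by sampling 40 clusters (doctors) with 26 patient questionnaires in each group". It assumes 0.28 in the control group and 0.34 in the intervention group, a two-sided unpooled Z test at 0.05 and an ICC of 0.005. The total of 4,160 questionnaires is 2 × 2,080, that is, one such sample at baseline and one at evaluation.

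**The concern.** These passages describe different primary analyses. A change needs both periods and a term that separates them. A regression on arm and site has no such term, so it cannot estimate a change whichever questionnaires are put into it:

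- With evaluation questionnaires only, it estimates a between-arm difference at evaluation.
- With both periods pooled, it mixes pre-intervention data into the arm effect and dilutes it.

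The text does not say which is meant. The sample size matches the first option, but the endpoint's name and the Setting sentence point to a before-and-after contrast.

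An evaluation-only comparison, a baseline-adjusted comparison and a difference in change can each be defended from some part of the text, and they can give different P values. The Limitations section says that participants and researchers are not blinded, so the choice should not stay open until data are seen. The power statement also depends on which analysis is run.

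**Working it through.** **Inputs from the Sample size calculation.** p0 = 0.28, p1 = 0.34, K = 40 doctors per arm, m = 26 questionnaires per doctor per period, ICC = 0.005, two-sided alpha 0.05. One yes/no outcome per questionnaire is taken, as the plan's Z test does.

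**Assumption not in the documents.** r is the correlation of a doctor's effect between the two periods. The full range 0 to 1 is shown.

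**Step 1: the plan's own figure (one time point).**
- p0(1−p0) = 0.2016; p1(1−p1) = 0.2244; sum 0.4260.
- Design effect = 1 + 25 × 0.005 = 1.125.
- SE = √(0.4260 × 1.125 / 1040) = 0.02147.
- Power = Φ(0.06/0.02147 − 1.96) = Φ(0.835) = 79.8%.

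The stated 80% is therefore the power of a two-group comparison in a single period.

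**Step 2: the same design tested as an unadjusted difference in change.** The four arm-by-period proportions are 0.28, 0.28, 0.28 and 0.34.
- Per-doctor factor: f = ICC + (1−ICC)/m = 0.005 + 0.995/26 = 0.04327.
- Variance = [(3 × 0.2016 + 0.2244) f − 2 r ICC (√(0.2016 × 0.2244) + 0.2016)] / 40.

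| r | SE | Variance relative to Step 1 | SE relative to Step 1 | Power |
|---|---|---|---|---|
| 0 | 0.02995 | 1.95 | 1.40 | 51.7% |
| 0.5 | 0.02907 | 1.83 | 1.35 | 54.1% |
| 1 | 0.02817 | 1.72 | 1.31 | 56.8% |

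Reaching 80% for that test would take 78.2 doctors per arm at r = 0 or 69.2 at r = 1, against 40 planned.

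**Step 3: evaluation-period comparison adjusted for the doctor's baseline percentage.** The approximate variance is that of Step 1 times (1 − c²), with c = r × ICC / f.
- ICC 0.005, r = 0: c = 0, power 79.8%.
- ICC 0.005, r = 1: c = 0.1156, SE = 0.02132, power 80.3%.

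**Step 4: sensitivity to a larger ICC (0.05, assumed).**
- Unadjusted, evaluation only: design effect 2.25, SE 0.03036, power 51%.
- Adjusted: 51% at r = 0, rising to 68% at r = 1 (c = 0.578, SE 0.02478).

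**The case against.** The strongest defence is that 'change' is loose wording. The only primary test that the protocol writes out is a between-group difference. The sample size section calls the same 0.06 a difference between group proportions and then, in the next sentence, an absolute change. The before-and-after sentence sits in a general Setting paragraph that also covers the doctor outcomes. On that reading the model and the sample size agree and the 80% stands. Much of this holds, and it limits the point. It does not remove it: the endpoint is called a change in three places, a full baseline round is collected, and no passage says which period is analysed. A separate SAP may exist, but the conflict is between statements in the protocol, so an SAP that follows the model departs from the named endpoint, and the reverse.

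A reader might infer stronger things that the documents do not support:

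- **That the planned test has only 52% to 57% power.** This figure belongs to an unadjusted difference in change, which the protocol never specifies.
- **That a change analysis doubles the sampling error.** At the plan's ICC the variance rises 1.72 to 1.95 times and the SE 1.31 to 1.40 times. At an assumed ICC of 0.05 and r = 1, the change analysis is more precise than evaluation-only (power 59% against 51%).
- **That omitting baseline does serious harm.** Randomisation keeps the evaluation-only comparison unbiased, and at ICC 0.005 adjustment adds at most about 0.5 percentage points of power.
- **That half of the questionnaires are discarded.** The text does not say which questionnaires enter the model, and baseline data also serve the comparison with nonparticipating doctors.

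One caveat on the figures stands. The Abstract can be read as a percentage of items per patient. With 14 items and an assumed inter-item correlation t of 0.5 to 0.9, the variance is multiplied by (1 + 13t)/14, or 0.54 to 0.91. Power for a change is then 56% to 83%, and for one time point 84% to 97%. The gap between the two analyses remains, but its level depends on the outcome definition.

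**Conclusion.** The point holds as a mismatch between the named endpoint, the model and the basis of the power statement. The 80% is correct for an evaluation-period comparison between arms and for nothing else in the text. If the endpoint were tested literally as an unadjusted difference in change, power would be about 52% to 57%, given one yes/no outcome per questionnaire, ICC 0.005, new patients in each period and any over-time doctor correlation from 0 to 1. The defect is an undefined primary estimand, not too few doctors. Adjusting for baseline is close to neutral on the plan's inputs. Its value is insurance against a larger ICC, and the size of that benefit rests on an ICC and an over-time correlation that the documents do not give.

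**What to change.** 1. Define one primary estimand: the between-arm difference in percentage 'excellent' among evaluation-period questionnaires.
2. Estimate it with the planned clustered binary regression, containing arm, site and the doctor's own baseline percentage 'excellent'. Amend the statement that excludes further covariates.
3. Replace the change wording in the Abstract (Methods), the Primary endpoint section and the Strengths part of the Discussion, and reconcile the before-and-after sentence under Setting. The Hypotheses section does not use the phrase and needs no edit.
4. State in the Sample size calculation that the 80% refers to the evaluation-period comparison, not to a difference in change.

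The cost is wording in the protocol and SAP plus one covariate. The Patients section reports that baseline questionnaires have been collected at all three sites, so no new data and no additional doctors are needed. The change should be fixed and dated before evaluation data are examined by arm.
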